## Abstract

**ABSTRACT:**

**Objectives:**

Proton pump inhibitors (PPIs) are widely prescribed medications and commonly used for the treatment of gastric acid-related disorders. Nevertheless, PPIs are often overused leading to potential adverse effects and unnecessary healthcare costs. Deprescribing strategies have emerged to safely reduce or substitute inappropriate PPIs and optimise patient care in an evidence-based manner. This protocol describes a study to evaluate the effectiveness of a PPI deprescribing intervention in comparison to usual care in the Swiss primary care setting.

**Design:**

An open-label, cluster randomised controlled trial.

**Setting:**

Swiss primary care settings.

**Participants:**

Included participants will be adults with inappropriate PPI treatment and will be recruited by general practitioners (GPs). Participants treated by the same GP constitute a cluster. Clusters are randomised 1:1 to either the intervention group or the control group.

**Interventions:**

The intervention components consist of deprescribing tools including educational material, decision aids for both participants and GPs, and additional trainings for GPs only. Patients in the control group will receive usual care. Data will be collected at baseline, 3-, 6-, 9- and 12-month follow-up time through online surveys or a phone call for both GPs and participants.

**Primary and secondary outcome measures:**

The first co-primary endpoint is the effectiveness of the deprescribing intervention measured by the change of prescribed PPI dose. The second co-primary endpoint is safety, which is measured with the Reflux Disease Questionnaire assessing change in gastrointestinal symptoms. There are several secondary endpoints, such as the total number of prescribed medications, occurrences of changes in prescription patterns, PPI discontinuation and cost-effectiveness.

**Conclusions:**

The findings from this study will provide evidence on the effectiveness and safety of a PPI deprescribing intervention for patients and GPs. Successful implementation of our PPI deprescribing strategy has the potential to improve patient outcomes and lower costs.

**Trial registration number:**

NCT06129474.

STRENGTHS AND LIMITATIONS OF THIS STUDYThis trial will test a context-specific, patient-centred intervention that draws on health psychology and behaviour change principles to support general practitioners (GPs) and patients in discontinuing proton pump inhibitors.Our intervention is designed to encourage and promote shared decision-making between patients and GPs.This trial encourages GPs to be inclusive and seek diversity among their recruited participants.We acknowledge that this trial would require less resources and less time from participants, GPs and other team members if there were electronic healthcare records databases available, but these are currently not available in Switzerland.Due to the nature of the intervention this trial will be open-label, which could introduce bias.

## Introduction

 Proton pump inhibitors (PPIs) are currently among the most frequently prescribed medications for the management of gastric acid-related disorders.^1^ Among others, they are used to treat gastro-oesophageal reflux disease (GORD), dyspepsia and reflux esophagitis, or for the treatment of ulcers associated with the use of non-steroidal anti-inflammatory medication (NSAIDs), and finally for *Helicobacter pylori* eradication in combination with antibiotics.^2^,^4^ According to a nationwide Swiss study, PPI prescription increased from 19.7% in 2012 to 23.1% in 2017.^4^ One-fourth of prescribed PPIs were characterised as inappropriate, either due to inadequate indication or too high doses.^4^ While PPIs are generally considered to have good short-term tolerance and an excellent safety profile^5^; the long-term use of PPIs is associated with adverse events, such as nutritional deficiencies,^6^,^8^ osteoporosis,^9^ fractures,^10^ intestinal infections with *Clostridioides difficile*, *Shigella*, *Campylobacter* or *Salmonella*,^11 12^ pneumonia,^13^ cancer^14 15^ and increased all-cause readmission,^16^ and healthcare costs.^17 18^

Deprescribing, which involves withdrawing, reducing the dose or substituting medications that are no longer beneficial or potentially harmful, is a well-established strategy for optimising medication use and minimising adverse effects.^19^ Despite the potential benefits of deprescribing PPIs, they are often not deprescribed in routine practice. A case vignette study in 31 countries found that PPIs were among the most common medications that general practitioners (GPs) were willing to deprescribe.^20^ A previous systematic review investigating different deprescribing strategies, reported that implementing a deprescribing intervention led to PPI discontinuation rates ranging between 14% and 64% without deteriorating symptoms.^21^ However, the studies included in this systematic review varied considerably in terms of study design and deprescribing interventions.^21^ Another study evaluating PPI deprescribing strategies in primary care highlighted two key factors associated with the success of the strategies (1) clarity and simplicity of the materials that patients receive and (2) training of the physicians.^22^ In addition, the acceptance of deprescribing depends highly on the setting, country and cultural attitudes towards medication,^23^ which underlines the importance of context-specific strategies including shared decision making between patients and their physicians.

Following the observed increase in inappropriate PPI prescriptions in Switzerland, a context-specific deprescribing intervention is expected to benefit healthcare and reduce unnecessary safety risks in patients.^24^ Therefore, we have developed a context-specific, patient-centred intervention that draws on health psychology and behaviour change principles to support GPs and patients in discontinuing PPIs, which we plan to test in a cluster-randomised clinical trial. The primary objective of our trial is to assess if the study intervention leads to the deprescribing of inappropriate PPIs (ie, effectiveness), while ensuring non-inferiority safety, in comparison to usual care, in adults in the Swiss primary care setting. Second, we aim to investigate the impacts of the intervention on other clinical outcomes, such as the number of medications used, quality of life (QoL), additional safety endpoints and costs. Alongside the trial, a cost-effectiveness analysis will be performed.

## Methods

### Methods: participants, interventions and endpoints

#### Trial design and setting

The DepRescribing inapprOpriate Proton Pump InhibiTors (DROPIT) trial is an open-label, cluster-randomised controlled trial conducted in primary care settings of German-speaking regions in Switzerland.

#### Study participants

Patients eligible for the DROPIT trial will receive regular care from a GP, be ≥18 years old, have sufficient knowledge of German and have a daily PPI intake for ≥8 weeks.

Exclusion criteria include a life-expectancy <12 months (as estimated by the GP), inability to provide informed consent by themselves or a legal representative, taking PPI in an appropriate dose and with an established indication (online supplemental A table S1 and online supplemental A table S2, online supplemental B patient informed consent forms). Similarly, patients are excluded if they have ≥2 of the following medications, or if they are using ≥1 of the following medications and have ≥1 of the risk factors mentioned below. Medications: chronic use of NSAID >7 days, antiplatelet therapy, additional antiplatelet therapy (eg, ticagrelor or similar), anticoagulation, systemic steroids >1 month. Risk factors: history of gastrointestinal ulcer, age ≥65 years, additional use of selective serotonin reuptake inhibitor or serotonin and norepinephrine reuptake inhibitor, severe concomitant disease with increased risk of gastrointestinal bleeding according to the GP’s assessment (ie, severe liver disease, neoplasia, severe misuse of alcohol and nicotine).

#### Study arms

##### Intervention components

The GPs in the intervention group receive the PPI deprescribing intervention tools and materials at the start of follow-up. The intervention is designed for the Swiss primary care setting and includes specific materials and tools for both GPs and trial participants (figure 1). It was developed to address the barriers and enablers of PPI deprescribing at patient and GP levels, and the materials were co-designed and adapted based on patient and GP feedback.^25^,^28^ For GPs, the intervention includes an initial digital and printable teaching module that provides comprehensive knowledge and skills related to PPI medications and the deprescribing process. This is followed by an online training session featuring interactive role plays to simulate various GP-patient scenarios. Additional material includes a laminated infographic, a consultation script and a deprescribing decision tree, all designed to assist GPs in guiding participants through the PPI deprescribing process. GPs will also be provided with a brochure to give to the trial participants (patients). This brochure contains information about PPIs, an explanation of the deprescribing process, a list of evidence-based alternative strategies to manage potential rebound symptoms and an invitation to use a digital symptom diary to self-monitor their symptoms and experiences throughout the trial. The digital diary requires internet access and a connection to the calendar on a cell phone or computer. For participants without internet access or a cell phone, a paper-and-pencil version of the symptom diary will be available.

**Figure 1 F1:**
[figure not shown]
Step-by-step implementation of the intervention.

On receipt of the intervention elements, the GPs are expected to use the teaching module, participate in the online training session, evaluate the participant’s PPI prescription and consult with the participant if needed (for which additional materials are provided). An overview of this process is depicted in figure 1.

##### Usual care

Participants and GPs in the control group receive and provide usual care, respectively, and do not have access to the intervention components. As part of standard care, GPs in the control group may evaluate and adjust their patients’ medications at their discretion.

### Follow-up

Follow-up will start the day of the delivery of the intervention (ie, delivery of the intervention materials to GPs), which should be within 30 days after cluster randomisation. In the control group, follow-up will start 15 days after cluster randomisation. Participants in both groups will be followed for 1 year, with data collection occurring at baseline and at 3, 6, 9 and 12 months after the start of follow-up. A detailed timeline for both trial arms is shown in online supplemental A figure S1.

### Study endpoints

#### Co-primary endpoints

There are two co-primary endpoints.

The first co-primary endpoint (superiority endpoint), evaluating the effectiveness of the intervention, is defined by the prescribed PPI dose as one minus the ratio between the average PPI prescription over the 12-month follow-up and baseline.The second co-primary endpoint evaluates safety (non-inferiority) using the Reflux Disease Questionnaire (RDQ). The RDQ is a self-administered questionnaire (12 questions) in which participants are asked to report the frequency and severity of their upper gastrointestinal symptoms using a 6-point scale ranging from 0 (no occurrence) to 5 (daily/severe) points per symptom. The RDQ includes three subscales: regurgitation, heartburn and dyspepsia. For the purpose of this endpoint, the dyspepsia and GORD (regurgitation combined with heartburn) subscales will be used.^29 30^

#### Secondary endpoints

The secondary endpoints are multifaceted: total number of medications prescribed during the trial measured using unique Anatomical Therapeutic Chemical codes, reduction of at least 50% of the prescribed PPI dose, PPI discontinuation (defined as a stop in PPI prescription as indicated by the GP), PPI sustained discontinuation (defined as 3 months without prescribed PPI), a switch to on-demand use, or use of alternative anti-reflux treatments, individual components of the RDQ (regurgitation, heartburn, dyspepsia) and atypical gastrointestinal symptoms measured by the Reflux Symptom Index (RSI).^31^ The RSI scales for each individual item ranges from 0 (no problem) to 5 (severe problem) points, with a maximum of 45 points. Further, we are interested in the occurrences of additional safety outcomes such as ulcers and/or gastrointestinal bleedings, nutritional deficiencies due to PPI overuse, such as vitamin B12, iron, magnesium or sodium, as well as other comorbidities, such as osteoporosis, small intestinal bacterial overgrowth, anaemia, fractures, nephritis and intestinal infections as reported by the GP. Furthermore, we will measure the QoL using the European Quality of Life-5-Dimensions 5-Levels (EQ-5D-5L) questionnaire.^32^ Each of the five dimensions (mobility, self-care, usual activities, pain/discomfort and anxiety/depression) has five levels (no, slight, moderate, severe and extreme problems) out of which one overall utility measure on a scale of 0 (worst health/death) to 1 (perfect health) will be derived using published algorithms.

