##### Statistical analyses for secondary and other endpoints

Repeatedly measured continuous secondary endpoints will be analysed using the same model as the safety co-primary endpoint. Count endpoints will be analysed with a generalised linear mixed model and a negative binomial distribution, accounting for the cluster’s random effect and observation time as an offset. Binary endpoints assessed at the end of the follow-up period will be analysed using mixed-effects logistic regression, adjusted for observation time, and including the cluster’s random effect. Cost-effectiveness analysis will employ generalised structural equation models. Finally, a descriptive summary of all pre-specified SAEs and deaths will be provided.

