## Discussion

The findings from this study will provide evidence on the effectiveness and safety of the DROPIT PPI deprescribing intervention. Successful implementation of our PPI deprescribing strategy could improve patient outcomes by reducing unnecessary adverse effects, such as infections, fractures or nutrient deficiencies, while ensuring appropriate, evidence-based treatment. Additionally, it could promote rational medication use, reduce polypharmacy, and minimise healthcare costs and resource utilisation. To our knowledge, this is the first randomised controlled PPI deprescribing trial in the primary care setting of Switzerland.

We chose a cluster-study design to prevent contamination that could arise if GPs were to treat participants in both the intervention and control groups.^42^ However, we recognise that cluster trials can introduce selection bias, as participant recruitment typically occurs after randomisation.^43 44^ To mitigate this, recruitment in our trial will cease once a cluster is closed, after which participants will be assigned to the intervention or control group based on their GP’s random assignment. It is unlikely that patients will avoid visiting their GP due to prior knowledge of the trial.

The 12-month follow-up period is consistent with similar studies and should be sufficient to capture potential rebound symptoms.^45^,^48^ Nevertheless, there is a small risk that we might miss the reoccurrence of GI bleeding or ulceration that might occur at a later time point, mainly because we are following the participants from the time we deliver the intervention to the GPs, which does not necessarily coincide with the timing of deprescribing. However, with a 12-month follow-up, and expecting that deprescribing will be done earlier rather than later during that time, we expect to observe the participant after the deprescribing.

Finally, we recognise that participants may receive new diagnoses during the follow-up period that justify PPI use, potentially no longer fulfilling the initial eligibility criteria. However, since this reflects typical clinical variations and occurs after randomisation, we will not exclude these participants. Instead, we may conduct a sensitivity analysis for the co-primary endpoints, where these participants will be censored.

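### The secondary endpoint on number of medications is a cumulative code count with a time offset, so a stopped PPI normally does not lower it and a substitute raises it

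*Protocol article*

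**What the plan says.** Under Secondary endpoints, the protocol article defines the outcome as the "total number of medications prescribed during the trial measured using unique Anatomical Therapeutic Chemical codes". Under Statistical analyses for secondary and other endpoints it states: "Count endpoints will be analysed with a generalised linear mixed model and a negative binomial distribution", with the cluster's "random effect and observation time as an offset". That section does not name this endpoint, but it is the evident count in the list.

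Three other statements determine how the count behaves. Eligible patients must "have a daily PPI intake for ≥8 weeks" (Study participants). "Follow-up will start the day of the delivery of the intervention", that is, when the materials reach the GP (Follow-up). The Discussion adds that this is a moment "which does not necessarily coincide with the timing of deprescribing".

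The Introduction names the number of medications used among the outcomes on which the intervention's impact is to be studied, and the Discussion hopes for less polypharmacy.

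**The concern.** A total over the trial of distinct codes, divided by observation time, reads naturally only as a cumulative count. Such a count can gain codes but never lose one already scored. The intervention works by removing a drug that every participant is taking at entry, so its main effect on the medication list is a subtraction that the endpoint normally does not see. A replacement drug is an addition, and that is seen.

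The offset is a separate difficulty. It makes the expected count proportional to time, which suits events that accrue, such as new prescriptions. Long-term medicines are on the list from day 0, so a shorter observation period inflates the rate without any change in treatment.

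At stake is the reading of this one endpoint. A null or slightly raised ratio could be reported as no effect on medication burden although fewer drugs were being taken at the end.

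**Working it through.** The article gives no expected value for this endpoint, so there is no figure to reproduce.

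**Inputs**
- Discontinuation: p = 0.10 control, 0.25 intervention (Sample size section).
- q = share of stoppers who receive a newly prescribed drug with its own code. Not given; taken over its whole range, 0 to 1, and equal in both arms. The article anticipates such drugs, since use of other anti-reflux treatment is itself a secondary endpoint.
- μ = mean number of other drugs, assumed equal in both arms. It cancels from the differences.

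**Step 1: expected counts per arm**
- Cumulative count, PPI still prescribed when counting starts: 1 + μ + pq.
- Count current at 12 months: 1 + μ − p + pq = 1 + μ − p(1 − q).

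**Step 2: intervention minus control**
- Cumulative: (0.25 − 0.10)q = +0.15q.
- Current: −(0.25 − 0.10)(1 − q) = −0.15(1 − q).

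| q | Cumulative | Current at 12 months |
|---|---|---|
| 0 | 0 | −0.15 |
| 0.3 | +0.045 | −0.105 |
| 0.5 | +0.075 | −0.075 |
| 1 | +0.15 | 0 |

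**Step 3: as ratios, assuming μ = 4**
- Cumulative: 5.00/5.00 = 1.00 (q = 0), 5.125/5.05 = 1.01 (q = 0.5), 5.25/5.10 = 1.03 (q = 1).
- Current: 4.75/4.90 = 0.97, 4.875/4.95 = 0.98, 5.00/5.00 = 1.00.

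A simulated negative binomial model (20,000 per arm, no cluster effect, no dropout) gave 1.00, 1.01 and 1.04 for the cumulative count and 0.97, 0.98 and 1.01 for the current count. This agrees apart from simulation error.

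**Step 4: the offset**
- A stable list of 6 drugs is 6/1 = 6 per year over 12 months, but 6/0.25 = 24 per year for someone who leaves at 3 months.
- Suppose, for illustration only, that 10% of the intervention arm and 5% of the control arm leave at 3 months. Mean observation time is 0.90 + 0.10 × 0.25 = 0.925 years and 0.95 + 0.05 × 0.25 = 0.9625 years. With equal counts (q = 0), codes over person-time give a rate ratio of 0.9625/0.925 = 1.04. The simulated negative binomial model gave 1.05.
- Reversed dropout: 0.925/0.9625 = 0.96 (simulated 0.96).
- Equal dropout: 1.00, no distortion between arms.

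**Step 5: if codes come only from the follow-up surveys**
Let e be the share of stoppers whose PPI is gone before the month-3 survey and so is never scored, equal in both arms. The cumulative difference becomes 0.15(q − e). At e = 0 this is Step 2; at e = 1 it equals the current count. In between it falls short: with q = 0.3 and e = 0.5 it is 0.15 × (−0.2) = −0.03, against −0.105.

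**The case against.** Several counter-arguments carry weight.

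- *A stopped PPI can sometimes register.* A reader might infer that the endpoint can never show a stop. The article does not support that. Follow-up medication data come at 3, 6, 9 and 12 months, and the Discussion expects stopping to happen early in the year. If codes are taken only from those surveys, a stop before month 3 lowers the count (Step 5). This stands, and the claim is limited to a PPI still prescribed when counting starts. Likewise, whether a switch to another PPI adds a code depends on the level of ATC coding, which is not stated.
- *The dropout effect is hypothetical.* A reader might infer that the offset biases the result against the intervention. It need not: the direction follows the assumed dropout and vanishes when loss is equal. The article states "Participants in both groups will be followed for 1 year" and expects little missing data, and medications are reported by GPs, so a patient's silence need not shorten the record. This limits the size, not the mis-specification.
- *The corrected endpoint may still be null.* Assuming SD 3.1, 360 patients, design effect 1.2 and a baseline correlation of 0.95, the standard error is 3.1 × √(4/360) × √1.2 × √(1 − 0.95²) ≈ 0.11. Even −0.15 is then only about 1.3 standard errors. This stands: the change makes the endpoint measure the right thing but does not make it well powered.
- *Polypharmacy is only an aspiration.* True of the Discussion, and the Introduction gives no direction. But impact on medications used is a stated aim, and a tally that normally ignores stopping answers it poorly.
- *Covariates belong in the analysis plan.* Agreed: the absence of a baseline adjustment is not itself a fault here. It appears only as part of the replacement.

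**Conclusion.** The point holds at moderate severity. Under the published definition, with the article's own discontinuation rates, PPI deprescribing contributes between 0 and +0.15 drugs to the between-arm difference, while the number of drugs actually current at 12 months changes by between −0.15 and 0. This rests on three conditions: the PPI is still prescribed when counting starts, q is the same in both arms, and other medicines are similar between arms. The offset adds a distortion only if early loss differs between arms; ratios of about 0.96 to 1.05 arise under the illustrative 5% and 10% loss at 3 months and have no firmer basis.

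A reader might take this as a threat to the trial's main conclusions. It is not: average PPI dose, symptoms, 50% dose reduction, discontinuation, sustained discontinuation and use of alternatives are all measured directly. Nor does it extend to the logistic models for binary endpoints, which also adjust for observation time. Those are different endpoints and a different use of the variable, and nothing shown here bears on them.

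**What to change.** Redefine the endpoint as the number of concurrently prescribed medications (unique ATC codes) at each visit. Take the between-arm difference at 12 months as the contrast, adjusted for the baseline count, with a cluster random effect and no time offset. The repeated-measures mixed model that the article already sets for continuous secondary endpoints could carry this. Newly started drugs may be reported separately; for that quantity a time offset is reasonable.

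The cost is a wording change to a listed secondary endpoint in the protocol and the registration, probably with notice to the ethics committee. No new data are needed, because GPs report medications at baseline and at every follow-up, and the first participant was still to be enrolled when the article was written.

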### Methods: data collection, management and analysis

#### Data collection

Data will be collected from participants and GPs at baseline and at 3-, 6-, 9- and 12-month follow-up. Baseline data will be collected within 60 days prior to group allocation (ie, cluster randomisation). Follow-up data from participants will be collected directly through surveys (operationalised by REDCap^40 41^), or alternatively by phone, based on participants’ preference. Data from GPs will be gathered at the same time points via online surveys (REDCap).

Data collected from patients will include demographics, characteristics, attitudes toward medications, endpoint data, assessment of the implementation of the intervention elements, healthcare utilisation and safety data. From GPs, we will collect eligibility confirmation, information on patients’ medications and diagnoses, assessment of the implementation of the intervention elements and reports of serious adverse events (SAEs).

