#### Statistical analysis

##### Statistical analyses for co-primary endpoints

To address the effectiveness, we will first quantify the change in prescribed PPI dose over the 12-month follow-up period. This will be done in two steps: (1) estimating the average PPI dose over the 12 months of follow-up, by dividing the area under the curve by the observation time and (2) calculating the relative change from baseline as one minus the ratio between the average prescription and the baseline prescription. Subsequently, the difference in the change in prescribed PPI dose between the control and intervention group will be calculated using a linear model, adjusted for the baseline dose and including a random effect for the cluster. We will use an intention-to-treat (ITT) analysis as primary analysis, and a per-protocol analysis as a secondary approach.

To address safety, the difference in the change in upper gastrointestinal symptoms between the two groups will be calculated with a repeated-measures linear mixed-effects model, adjusted for baseline values, and including the intervention group, the timepoint, and the interaction between group and timepoint as fixed effects. Effects of the cluster and participant will be added as random effects. We will conduct both ITT and per-protocol analyses. To claim success for the safety co-primary endpoint, both ITT and per-protocol analyses need to meet non-inferiority.

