### Limitations

Neither participants nor GPs in the intervention group or study team members/data analysts will be blinded due to the trial design. The data collected through the online survey by the participants heavily depend on the response rate. To the best of our ability, we will try to send online reminders to both participants and GPs to complete the survey.

One could hypothesise that the GPs participating in a deprescribing study may be more attentive to reducing inappropriate prescribing. However, in the study by [name] *et al* from our team, we observed that when GPs were instructed to actively identify inappropriate PPIs in patient records, only 35% of the inappropriate PPIs were stopped or reduced after 12 months, while over 60% remained unchanged.^24^ Reasons for a failed deprescribing included lack of discussion with patients, their unwillingness to stop, and fear of recurrence of symptoms. Therefore, it cannot be excluded that an increased awareness among control group patients will bias the trial results towards the null, but the effect is likely to be small.

Each GP is treated as a separate cluster and GPs are requested to keep confidentiality with colleagues. This is particularly relevant when several trial GPs work in the same practice. Otherwise, a contamination across GP clusters may potentially bias the trial results toward the null hypothesis, underestimating the intervention effect. However, GPs are used to maintaining confidentiality among colleagues and have little time to discuss the trial with peers, thus we trust that group contamination will be minimal.

In Switzerland, low dose PPI are available over the counter in pharmacies. While we will ask participants to report any self-administered medications that were not prescribed, we cannot completely control whether they purchase and use PPIs independently without reporting them. However, this issue is not expected to differ between the two groups.

There might be the possibility of a slight reporting bias as the participant surveys include questions about upper gastrointestinal symptoms. Therefore, participants could be more aware of upper gastrointestinal problems during the trial period and report these more frequently.

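### The secondary endpoint on alternative anti-reflux treatments does not set aside use already present at baseline, and the model that presumably applies to it has no baseline term

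*Protocol article*

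**What the plan says.** The Secondary endpoints section lists several outcomes that describe what happens to the PPI prescription: a dose reduction of at least half, discontinuation, sustained discontinuation, and then "a switch to on-demand use, or use of alternative anti-reflux treatments". The last item carries no qualifier such as new or started.

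Under Statistical analyses for secondary and other endpoints, binary outcomes at the end of follow-up are to be "analysed using mixed-effects logistic regression, adjusted for observation time, and including the cluster’s random effect". No baseline term is named. By contrast, under Statistical analyses for co-primary endpoints, the effectiveness model is "adjusted for the baseline dose and including a random effect for the cluster", and the safety model is a "repeated-measures linear mixed-effects model, adjusted for baseline values". The safety model is also used for repeatedly measured continuous secondary endpoints.

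The Study participants section requires daily PPI intake for at least 8 weeks. It does not list existing use of another anti-reflux treatment among the exclusions.

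On data, the article states: "Data will be collected from participants and GPs at baseline and at 3-, 6-, 9- and 12-month follow-up". Patients' medications are among the items collected from GPs. The Limitations section adds that "we will ask participants to report any self-administered medications that were not prescribed".

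**The concern.** For the neighbouring endpoints, eligibility puts everyone in the same starting state: on a daily PPI. A stop, a switch to on-demand use or a halving of the dose is then a change from entry by construction, and a model without a baseline term is reasonable. Use of an alternative treatment is the exception. Its baseline state is not fixed by eligibility, not addressed by the wording of the endpoint, and not addressed by the stated model.

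A participant who took another anti-reflux product beside the PPI before randomisation and simply carries on could therefore be an event in either arm, although nothing changed. Such events add the same amount to both arms in expectation and carry no information about the intervention. At stake is how well this endpoint can show a shift to other treatments, which helps in reading the dose and symptom results.

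**Working it through.** **1. Inputs from the article (Sample size; Cluster-randomisation and group allocation).** Rates of 10% v 25%, two-sided alpha 0.05, power 90%, intracluster correlation 0.05, 80 clusters, coefficient of variation of cluster size 0.5, target 400 patients, 1:1 allocation. The article gives no figure for the alternative-treatment endpoint.

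**2. Reproducing the article's own figure.** Two-proportion formula with pooled null variance and no continuity correction, both arms together:

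N = 2 × [1.96 × √(2 × 0.175 × 0.825) + 1.2816 × √(0.10 × 0.90 + 0.25 × 0.75)]² / 0.15² = 265.5 before clustering.

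Design effect: DE = 1 + (1.25 m − 1) × 0.05, with 1.25 = 0.5² + 1. Solving 80 m = 265.5 × DE gives m = 3.98 and N = 318, against 4.0 and 316 stated. The method matches the plan closely enough to use below.

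**3. Design for the illustration.** With 400 participants in 80 clusters, m = 5 and DE = 1 + (6.25 − 1) × 0.05 = 1.2625. The effective size is 400 / 1.2625 = 316.8, or 158.4 per arm.

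**4. Assumptions that the article does not supply.**
- Baseline prevalence of alternative treatment: q, shown as a range.
- New use among baseline non-users: 10% v 25%. These are the article's discontinuation rates, borrowed only to have a scale.
- Baseline users all continue, in both arms.

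**5. If any use counts.** The event rate in an arm is q + (1 − q)p, with p = 0.10 or 0.25. The difference is (1 − q) × 0.15. At q = 0.20 the rates are 0.20 + 0.80 × 0.10 = 0.28 and 0.20 + 0.80 × 0.25 = 0.40, so the difference is 0.12 and the odds ratio (0.40/0.60)/(0.28/0.72) = 1.71.

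Full continuation is not needed for the shrinkage factor. If baseline users have any common event rate c in both arms, the term qc cancels and the difference is still (1 − q) × 0.15. It does affect the odds ratios and the power.

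**6. If only new use among baseline non-users counts.** The rates stay at 10% v 25% (odds ratio 3.00), on 400(1 − q) participants. Power is given twice: with the design effect held at 1.2625, and with mean cluster size reduced to 5(1 − q).

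| Baseline use q | Any use, control v intervention | Difference (points) | Odds ratio | Power, any use | Power, new use (DE held / m reduced) |
|---|---|---|---|---|---|
| 0% | 10.0% v 25.0% | 15.0 | 3.00 | 94% | 94% / 94% |
| 10% | 19.0% v 32.5% | 13.5 | 2.05 | 79% | 92% / 93% |
| 20% | 28.0% v 40.0% | 12.0 | 1.71 | 62% | 89% / 90% |
| 30% | 37.0% v 47.5% | 10.5 | 1.54 | 47% | 84% / 87% |

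**The case against.** **The text may already mean a change.** The Abstract summarises this group as "occurrences of changes in prescription patterns, PPI discontinuation and cost-effectiveness", and the phrase in the endpoint list can be read as a switch to on-demand use or to alternatives. Nothing in the article says that prevalent users are counted. This stands: the wording leaves the matter open. It also supports the fix, because if change is meant, neither the word *use* nor the stated model secures it.

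**The detail may sit in the full protocol or analysis plan.** That is possible, and the article does not expressly call this endpoint binary, so applying the logistic model to it is an inference. The point therefore rests on what the article does state: an endpoint word and a class of model that do not fit together for this one item.

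**The numbers are borrowed.** This is correct. Prevalence, new-use rates and continuation are all assumed, and the trial was not sized for this endpoint, so no stated power target is missed.

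**The covariate remedy could fail.** If every baseline user continues, a yes/no baseline covariate predicts the outcome perfectly in that group, and the logistic fit runs into quasi-complete separation. That happens only in this extreme case, and even then the treatment estimate is carried by the baseline non-users.

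**A stronger reading that the documents do not support.** A reader might infer that the dilution flatters the intervention by hiding replacement of the PPI. Randomisation balances prevalent use in expectation, so what is lost is sensitivity. The Abstract and Introduction also count substitution as part of deprescribing, and the patient brochure offers alternative strategies for rebound symptoms. A shift to alternatives is thus partly intended, and dilution could equally understate an intended effect.

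**Conclusion.** The concern holds as a gap in one secondary endpoint. Neither eligibility, the endpoint wording nor the model that presumably applies deals with use at baseline. If prevalent use is counted and baseline users have the same event rate in both arms, the risk difference is multiplied by (1 − q). Under the illustrative assumptions the loss of power runs from nil at q = 0 to roughly 28 percentage points at q = 20% (about 62% against about 90%), and more above that. The true size cannot be known from the article.

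It should not be put as a statement that the endpoint does count prevalent users, since the text permits either reading. The dose and RDQ co-primary analyses do not depend on this endpoint and are unaffected. The point is minor.

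**What to change.** In Secondary endpoints, define the outcome as new use of an alternative anti-reflux treatment, meaning one not in the participant's baseline medication record. This matches the Abstract's description of the group as changes. Alternatively, keep the present wording and all participants, and add baseline use (yes/no) as a covariate in the logistic model for this endpoint. In either case, report baseline use by arm.

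The cost is a change of wording in the protocol and analysis plan, since medications are already collected at baseline and at each follow-up. There are two things to weigh:

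- Under the new-use definition, continuing or increasing a treatment held at baseline is not an event. The covariate version keeps these participants in the analysis, but a yes/no outcome still cannot tell an increase from mere continuation.
- The article says that participants will be asked about self-administered products, but not that this is done at baseline. Baseline recording of over-the-counter products should be confirmed, because otherwise old use could be classed as new.
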